## Abstract

**Background:**

Childhood undernutrition remains a public health issue that can lead to unfavourable effects in later life. These effects tend to be more devastating among urban poor young children, especially in light of the recent COVID-19 pandemic. There is an immediate need to introduce interventions to reduce childhood undernutrition. This paper described the study protocol of a nutrition programme that was developed based on the positive deviance approach and the evaluation of the effectiveness of the programme among urban poor children aged 3 to 5 years old.

**Methods:**

This mixed-method study will be conducted in two phases at low-cost flats in Kuala Lumpur. Phase one will involve a focus group discussion with semi-structured interviews to explore maternal feeding practices and the types of food fed to the children. Phase two will involve a two-armed cluster randomised controlled trial to evaluate the effectiveness of a programme developed based on the positive deviance approach. The programme will consist of educational lessons with peer-led cooking demonstrations, rehabilitation, and growth monitoring sessions. Intervention group will participate in the programme conducted by the researcher for three months whereas the comparison group will only receive all the education materials and menus used in the programme after data collection has been completed. For both groups, data including height, weight, and dietary intake of children as well as the nutritional knowledge and food security status of mothers will be collected at baseline, immediate post-intervention, and 3-month post-intervention.

**Expected results:**

The positive deviance approach helps to recognise the common feeding practices and the local wisdom unique to the urban poor population. Through this programme, mothers may learn from and be empowered by their peers to adopt new feeding behaviours so that their children can achieve healthy weight gain.

**Trial registration:**

This study was registered with clinicaltrials.gov: NCT04688515 on 29 December 2020, https://www.clinicaltrials.gov/ct2/show/NCT04688515.

## Introduction

Child undernutrition can manifest in three main forms, namely underweight, stunting, and wasting. Globally, 149.2 million children under-five (22.0%) were stunted while another 45.4 million children (6.7%) were wasted in 2020 [1]. The estimated global prevalence of underweight was also high at 12.6% in 2020 [2]. In Malaysia, the prevalence of stunting is showing an increasing trend from 20.7% in 2016 [3] to 21.8% in 2019 [4]. Likewise, the same rising trend was also observed in the prevalence of underweight children whereby it increased from 13.7% in 2016 [3] to 14.1% in 2019 [4]. On the other hand, the prevalence of wasting decreased by 2.1% from 11.5% in 2016 [3] to 9.4% in 2019 [4]. Although the prevalence of wasting was declining, the latest national prevalence of undernutrition among children under-five continued to be high. With the alarming trend of persistent undernutrition among children in Malaysia, there is an immediate need to introduce effective strategies to mitigate this national problem.

In view of the COVID-19 pandemic, urban poor populations, particularly children, are becoming even more susceptible to malnutrition. Significant deterioration in nutritional status among them is likely compared to before. Prior to the pandemic, the low-income population already suffered immensely because they reside in high-cost urban areas. In the aftermath of socioeconomic crisis due to the Movement Control Order (MCO) implemented in the country to control the spread of COVID-19, the urban poor population faces even more hardship and struggle to survive [5]. Young children living in urban poor families are likely exposed to an even higher risk of undernutrition because financially-stricken parents might cut down on meal frequency and diet quality to cope with the economic hardship following the pandemic. In view of this, it is vital to further strengthen the intervention programme and to scale up any actions needed to address the worsening issue of undernutrition among children.

Intervention studies aimed at reducing undernutrition among Malaysian children under-five are still lacking. Most local intervention studies focused on childhood obesity among school children [6–11], or undernutrition among indigenous children [12]. However, similar issues among urban poor children are rarely addressed, perhaps due to the perception that residents in urban areas are likely to be wealthier with better living standards. Besides that, nutritional interventions targeting undernourished children are usually implemented in traditional methods such as the provision of supplemental foods [13–15], growth monitoring [16, 17], and micronutrient supplementation [18–20]. Such approaches would subject financial burden on the government and also create unwanted dependency on the external aid among the communities. Relying solely on food supplementation from external assistance without proper education is insufficient to address nutritional issues among the vulnerable population. A more effective intervention strategy should incorporate positive behavioural changes that can support the targeted community in actively seeking practical solutions in their local setting.

In light of this, the introduction of more inventive approaches is deemed necessary to enhance the impact of the intervention. Since the daily diet of young children is mainly controlled by their mothers [21], maternal feeding practices play a vital role in the solution of the undernutrition issue. Hence, innovative interventions such as the positive deviance (PD) approach that encourage positive and sustainable change in maternal behaviours when feeding their children can highly effective in reducing undernutrition among children under-five.

The PD is described as any uncommon outlying yet successful norms, behaviours, or practices that may be beneficial and able to successfully solve the community problem [22]. The approach focuses on recognising the PD that causes a person to outperform others in the same community [23]. Such practice is eventually shared within the community to deal with the community’s problem [24]. This approach also emphasizes on the application of culturally-acceptable solutions in the local setting that can potentially promote positive behavioural changes among mothers. Eventually, it is hoped that they will take the necessary initiatives to achieve healthy weight gain in their children.

To date, there is a lack of local studies on interventions that encourage positive and sustainable behavioural changes that can improve child nutritional status among primary caregivers of young children. Elsewhere, a few intervention studies are using the PD approach to improve the nutritional status of undernourished children in countries such as Ecuador, Ethiopia, and Burundi [25–29]. Nonetheless, mixed findings have been shown in other countries. A few studies showed that the approach was successful in improving nutritional status with a reduction in undernutrition prevalence, significant weight gain, and increased nutrient intake of children while some studies showed no effect [24, 30, 31]. Apart from the positive outcomes in terms of growth and nutrient intake, the effectiveness of a PD programme in improving other aspects such as food security status and nutritional knowledge of mothers remains unknown.

Therefore, this study aims to describe the study protocol of a nutrition programme on urban poor children using the PD approach. Firstly, the PD behaviours of the urban poor households will be identified and subsequently these findings will be applied to develop a locally and culturally-acceptable solution to tackle the child undernutrition issue among the urban poor. These solutions include a combination of nutrition education with peer-led cooking session and promotion of positive behavioural changes among caregivers of young children. The objectives of this study are to explore maternal feeding practices and foods that are fed to children of both positive deviant (PD) family (poor family with well-nourished children) and non-positive deviant (NPD) family (poor family with undernourished children) as well as to evaluate the effectiveness of the programme in reducing undernutrition among urban poor children aged 3 to 5 years old.

## Materials and methods

The underlying protocol follows SPIRIT Statement (S1 Checklist) and CONSORT Checklist (S2 Checklist).

### Study design

This is a mixed-method study that involves both qualitative and quantitative methods. In phase one of the study, a qualitative research method will be used while in phase two, a two-armed cluster RCT will be conducted. The primary outcome of the RCT study will be weight-for-age z-score (WAZ), while the secondary outcomes will include height-for-age z-score (HAZ), weight-for-height z-score (WHZ), nutrient intake, diet quality, food security status and nutritional knowledge of mothers. The study population includes 3 to 5 years old children with their mothers who live together in the low-cost PPR flats in Kuala Lumpur. Children aged 3 to 5 years old are recruited because when compared to younger children (<2 years old), older children are at higher risk of undernutrition [32].

#### Phase 1 (qualitative study)

In the first phase of the study, the identification and classification of families into PD family and NPD family based on the children’s anthropometric measurements will be first carried out. Following that, a qualitative study in the form of focus group discussion (FGD) with semi-structured interviews will be conducted. The inclusion criteria for the participants in Phase I, i.e. the mothers are: Malaysians, above 18 years old with children aged 3 to 5 years old, living in low-cost PPR flats and with a monthly household income of <RM3000. The monthly household income is set at RM3000 because this is the requirement to apply for residing in a public low-cost PPR flat [33]. For a household with more than one child aged 3 to 5 years old, the oldest child will be recruited as the index child. This is because older children have more autonomy in their daily diet, causing them to have higher chances of undernutrition compared to younger children [21]. Mothers whose children are taken care of by other adults will be excluded. Mothers whose children are diagnosed with chronic diseases, under treatment for communicable disease, learning disabilities will also be excluded as these children may have different eating habits and nutritional status, thus possibly contributing to a biased outcome. Apart from that, mothers with overweight or obese children (WHZ > +2SD) will also be excluded. Lastly, mother-child dyads who are involved in any other intervention or clinical research, mothers with mental disabilities, and mothers with low literacy level to fully understand the content of the questionnaires will also be excluded as they might not be capable to follow and involve completely in the present study.

A list of flats under the People’s Housing Project in Kuala Lumpur will be acquired from the Kuala Lumpur City Hall. By using the purposive sampling method, two flats with the top two highest number of housing units will be chosen. Then, the researcher will contact the chairperson of the community representative committee to obtain a list of households with children aged 3 to 5 years old. Household visits will be made to the selected flats. Purposive sampling will be used to select the subjects with well-nourished or undernourished child. Two focus groups will be recruited from the PD family [family with well-nourished under-five child who has normal growth indicators (-2SD≤Z≤ +2 SD for WAZ, HAZ and WHZ)] while another two from the NPD family [family with undernourished child who is either underweight, stunting or wasting (WAZ/HAZ/WHZ<-2SD)], with each group consists of 6 participants. Thus, the estimated number of participants will be 24 or the participants will be interviewed until a saturation point is reached. Data saturation is considered reached when no additional insights can be identified from the participants and data start to be repetitive.

Before the interview, the participants will be approached to obtain their informed consent and permission for audio-recording. A short briefing will be given to the participants. After that, semi-structured face-to-face interviews in the form of FGDs will be held in the community hall in the flat. The researcher serves as a moderator to regulate the whole process of the FGDs. Every informant in the group will be given a chance to answer each question. Each session of FGD will take approximately one hour. An interview protocol, including a script and a list of questions pertaining to maternal feeding practices, will be prepared in advance. The examples of questions are “*What food did you usually feed your child in the morning*, *noon and evening*?*”* and “*What do you do when your child does not want to eat*?”.

After collecting the qualitative data, thematic analysis [34, 35] with NVivo 12 (Melbourne, Australia), which is the computer-assisted qualitative data analysis software (CAQDAS), will be used to analyse the data. Peer debriefing and data source triangulation will be performed. To perform data triangulation, multiple data sources will be collected from two different groups, namely the PD family and NPD family, to obtain information on feeding practices and food being fed to their children.

#### Phase 2 (quantitative study)

A two-armed, cluster randomised controlled trial will be carried out to determine the effectiveness of a nutrition programme. The selection criteria for respondents in this phase will be almost similar to those in Phase 1, except for one criterion related to children. In Phase 2, only undernourished children (either underweight, stunting, or wasting) aged 3 to 5 years old will be recruited to evaluate the effectiveness of the intervention programme in this particular group. The WHO Child Growth Standards for children under 5 will be used to classify children into underweight (WAZ< -2SD), stunting (HAZ< -2SD) and wasting (WHZ< -2SD) [36]. The exclusion criteria in Phase 2 are similar to the exclusion criteria in Phase 1.

### Sample size estimation

Sample size will be calculated using the formula for a RCT comparing two groups of equal size [37, 38], two-tailed test with 80% power and 5% significance level. As there was minimal information on the nutritional status of urban poor children and the effectiveness of nutrition programme in the setting of Malaysia, this study used the information obtained from a previous study that was not done in Malaysia but was using PD approach and it is relevant to the context of the present study [25]. By referring to the mean and SD of the WAZ of children aged 36 to 48 months in the intervention (using the PD approach) and comparison groups from a previous study [25], the minimum sample size required will be 28 in each group. It is estimated that there are around 10 households with undernourished children under five in a cluster of PPR flat. Thus, the cluster size per arm, m, is assumed to be 10 and the intra-cluster correlation coefficient (ICC) is assumed to be 0.03 [39]. Hence, with a calculated design effect of 1.27 and a non-response rate of 20%, the sample size is increased to 41 in each group.

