### Sampling

In Phase 2, the sampling will be based on the similar list of flats and households used in Phase 1, i.e. the two PPR flats with the highest and second-highest number of housing units. A total of fourteen flats, seven each for intervention and comparison groups, will then be chosen using a simple random sampling. Cluster randomisation will be performed to reduce the chance of contamination. Each flat is a cluster unit. Since the area of PPR flats in Kuala Lumpur is classified into four zones, residents from two zones will be randomly selected as intervention groups while another two zones as comparison groups. Then, by using the list of households with children aged 3 to 5 years old from the seven targeted flats in the respective zones, household visits will be carried out again to conduct anthropometric measurements on the children to obtain a list of households with undernourished children. After that, the mother-child dyads from the list who meet the inclusion and exclusion criteria will be number coded by the researcher and randomly selected to participate in the present study. The randomization process will be conducted using a computer-generated software (www.randomizer.org) by an independent third party. Participants (n = 82) will be randomized using permuted block randomization into two groups: intervention or comparison group in a 1:1 ratio.

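### The stated 80% power makes no allowance for seven flats per arm; if flats are the randomised unit, power at the planned loss is about 70% to 77%

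*Protocol article*

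**What the plan says.** The Sample size estimation section starts from an individually randomised comparison ("Sample size will be calculated using the formula for a RCT comparing two groups of equal size"), with a "two-tailed test with 80% power and 5% significance level". From the WAZ means and SDs of a cited study, which the article does not print, it concludes that "the minimum sample size required will be 28 in each group". For clustering, "the cluster size per arm, m, is assumed to be 10 and the intra-cluster correlation coefficient (ICC) is assumed to be 0.03". The result is that "with a calculated design effect of 1.27 and a non-response rate of 20%, the sample size is increased to 41 in each group". Nothing in the section refers to the number of clusters.

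That number is in the Sampling section: "A total of fourteen flats, seven each for intervention and comparison groups, will then be chosen using a simple random sampling". The section names the flat as the cluster unit. It then also says that two of the four zones are randomly selected for intervention and two for comparison, and that the 82 participants are randomised 1:1 in permuted blocks.

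**The concern.** Multiplying an individual-level sample size by a design effect corrects the variance of the arm difference. The result reaches its nominal power only if the between-cluster variance is known or is estimated from many clusters. With seven flats per arm, a test against between-flat variation uses a t reference with 12 degrees of freedom and a critical value of 2.179 in place of 1.960. The sizing does not include that penalty, so the stated power is too high for such a test.

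At stake is how a null result is read. It would be taken as coming from a trial with 80% power for the planned WAZ difference, when the design as printed may offer noticeably less.

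**Working it through.** **Inputs from the article.** Base n = 28 per group, two-sided 5%, 80% power, m = 10, ICC = 0.03, design effect 1.27, non-response 20%, final n = 41 per group (all Sample size estimation); seven flats per arm (Sampling).

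**Reproducing the plan's figures.**
- Design effect: 1 + (10 - 1) × 0.03 = 1.27, as printed.
- 28 × 1.27 = 35.56. Multiplying by 1.2 gives 42.67, so 43. Dividing by 0.8 gives 44.45, so 45. The printed 41 is close to the first but equals neither; 27 × 1.27 × 1.2 = 41.1 would give it.

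**Effect size (assumption).** The means and SDs are not printed, so the standardised difference d is solved back from n = 28:
- normal formula: d = (1.960 + 0.842) × √(2/28) = 0.749;
- t-based formula with 54 df: d = 0.762.

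**Power on cluster degrees of freedom.** Effective size n_eff = N / DE, noncentrality = d × √(n_eff/2), noncentral t with 2 × 7 - 2 = 12 df. Completers per arm: 41 × 0.8 = 32.8. Over seven flats that is 32.8/7 = 4.69 per flat, so DE = 1 + 3.69 × 0.03 = 1.11.

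| Case (per arm) | DE | n_eff | Power, normal reference | Power, 12 df |
|---|---|---|---|---|
| 35.56 analysed (the sizing's own target) | 1.27 | 28.0 | 80.0% to 81.4% | 73.0% to 74.5% |
| 41 recruited, 20% lost | 1.27 | 25.8 | 76.8% to 78.2% | 69.5% to 71.1% |
| 41 recruited, 20% lost, seven flats | 1.11 | 29.5 | 82.1% to 83.4% | 75.2% to 76.7% |
| 41 recruited, no loss | 1.27 or 1.15 | 32.3 or 35.8 | 85.3% to 89.7% | 78.8% to 84.1% |

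Each range runs from d = 0.749 to d = 0.762. In the last row, 41/7 = 5.86 per flat gives DE = 1 + 4.86 × 0.03 = 1.15. In the third row the normal reference would exceed 80%, so the shortfall there is due to the degrees of freedom alone.

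**Sensitivity to the ICC** (32.8 completers in seven flats, 12 df): 78.0% to 79.5% at ICC 0.01, and 66.3% to 67.9% at ICC 0.10.

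**If zones are the randomised unit.** Two against two leaves 2 df. The second and third rows then give 33% to 34% and 37% to 38%, even if zones add no variance of their own.

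**The case against.** **The unit of randomisation is not settled.** The Sampling section supports flats, zones and individuals in turn. If individuals were randomised, the 12 df would not necessarily apply. If zones were, the position is far worse. This stands, and it makes the 70% to 77% conditional on flats. Flats are nevertheless the natural reading for the sizing: the article calls Phase 2 cluster randomised, names the flat as the cluster and bases its design effect on children per flat. A reader might infer from the zone sentence that the trial has only about a third of the power it needs. The documents do not establish that, because they do not settle that zones are the allocated unit.

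**One figure of 73% is tempting but fits no single design in the article.** It pairs a design effect for 10 children per flat with seven flats per arm. Seven flats of 10 would be 70 children per arm, not 41. A range is the honest statement.

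**Baseline adjustment could recover the loss.** WAZ is measured at baseline, and adjusting for it would raise the power. With 12 df, 80% power needs a noncentrality of 3.053. At d = 0.749 the planned-loss noncentralities are 2.691 (DE 1.27) and 2.877 (DE 1.11). The baseline correlation needed is √(1 - (2.691/3.053)²) = 0.47 or √(1 - (2.877/3.053)²) = 0.33. Such values may well be reached, but the article states neither a correlation nor a baseline adjustment, and its sample size does not rely on one. So the figures here describe an unadjusted comparison. A reader should not infer that every possible analysis of this design falls below 80%.

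**A mixed model may use more degrees of freedom** when the estimated flat variance is zero, so realised power could be somewhat higher. That is fair, but the Statistical analysis section names no such model.

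**Conclusion.** The point holds in conditional form. If flats are randomised, a 12 df test with 41 per group and the planned 20% loss has about 70% to 77% power: 70% to 71% at the printed design effect, and 75% to 77% at the one that seven flats imply. All of these are below the stated 80%. The figures rest on a back-solved effect, an ICC of 0.03 and an unadjusted comparison. With no loss at all, power would be about 79% to 84%, but the plan itself allows for loss.

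This is a moderate shortfall that should be corrected in the stated power. It does not show that the trial cannot answer its question.

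**What to change.** Keep the enrolment. First reconcile two things:
- in the Sampling section, whether the flat, the zone or the participant is randomised;
- between Sample size estimation and Sampling, the cluster size (10 per flat, against 41/7, or about 6 recruited per flat).

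Then restate the power with degrees of freedom taken from the number of randomised units: about 70% to 77% on 12 df if flats, or about 33% to 38% on 2 df if zones. Once the cluster size is settled, the range for flats narrows to one of its two ends. If baseline adjustment is intended, state it together with the correlation assumed.

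In the analysis, test the arm effect against a matching small-sample reference, such as a t-test on flat means or a mixed model with a small-sample correction.

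The cost is a less favourable stated power and slightly more analysis work. No extra participants are needed.
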